## Abstract

**Background:**

The occupational therapy (OT) in care homes study (OTCH) aims to investigate the effect of a targeted course of individual OT (with task training, provision of adaptive equipment, minor environmental adaptations and staff education) for stroke survivors living in care homes, compared to usual care.

**Methods/Design:**

A cluster randomised controlled trial of United Kingdom (UK) care homes (n = 90) with residents (n = 900) who have suffered a stroke or transient ischaemic attack (TIA), and who are not receiving end-of-life care. Homes will be stratified by centre and by type of care provided and randomised (50:50) using computer generated blocked randomisation within strata to receive either the OT intervention (3 months intervention from an occupational therapist) or control (usual care). Staff training on facilitating independence and mobility and the use of adaptive equipment, will be delivered to every home, with control homes receiving this after the 12 month follow-up.

Allocation will be concealed from the independent assessors, but the treating therapists, and residents will not be masked to the intervention. Measurements are taken at baseline prior to randomisation and at 3, 6 and 12 months post randomisation. The primary outcome measure is independence in self-care activities of daily living (Barthel Activities of Daily Living Index). Secondary outcome measures are mobility (Rivermead Mobility Index), mood (Geriatric Depression Scale), preference based quality of life measured from EQ-5D and costs associated with each intervention group. Quality adjusted life years (QALYs) will be derived based on the EQ-5D scores. Cost effectiveness analysis will be estimated and measured by incremental cost effectiveness ratio. Adverse events will be recorded.

**Discussion:**

This study will be the largest cluster randomised controlled trial of OT in care homes to date and will clarify the currently inconclusive literature on the efficacy of OT for stroke and TIA survivors residing in care homes.

**Trial registration:**

ISRCTN00757750

## Background

A systematic review and meta-analysis by Legg et al. [1] of nine trials (1258 participants) found that in stroke survivors, occupational therapy (OT) increased personal activities of daily living scores (i.e., standardised mean difference 0.18; 95% confidence interval 0.04 to 0.32; p = 0.01). Furthermore, for every 100 people who received OT after a stroke, 11 (95% confidence interval 7 to 30) would be spared a poor outcome (i.e., death, deterioration in personal activities of daily living or dependency on others; Odds ratio 0.67; 95% confidence interval 0.51 to 0.87; p = 0.003). A care setting where OT might be particularly beneficial is in care homes, where 20% to 40% of all people newly admitted have stroke-related disabilities as their admittance diagnosis [2,3]. Generalisation of results from community studies should be treated with caution, as the characteristics of stroke survivors resident in a care home are likely to be different to those living in their own homes. For instance, 78% of residents in a care home have cognitive impairment, 76% need some form of assistance with ambulation and 71% are incontinent [2]. These factors might affect the capacity of care home residents to engage in OT.

OT in care homes has been embraced in countries such as The Netherlands, where 93% of residents regularly receive this form of therapy [4], in contrast to the United Kingdom (UK), where as few as 3% of residents in care homes receive OT [5]. Over the last decade, the government in the UK has established a framework to assess eligibility and prioritise care needs of residents [6,7]. However, a recent audit of 112 care homes in the Midlands area of the UK found that only 6% of homes used the services of an OT at least once a week [8]. The under-utilisation of OT in this setting might be the result of staff being unaware of the role of an occupational therapist and/or how to access the services. Conversely, from a service commissioner’s perspective there is little evidence that the provision of OT services for care homes residents following a stroke is effective and/or cost-effective [8].

In the literature there is conflicting evidence on the efficacy of OT for on activities of daily life in care homes residents with stroke-related disabilities [9-11]. For instance, a study by Sackley et al. [9], which involved 249 care homes residents with mobility limitations, found that after a three month OT and physiotherapy programme there was no measureable improvements in functional independence and mobility. Although the findings suggest the therapy intervention to be ineffective, it could be argued that therapists in this study delivered interventions to maintain physical abilities of the residents rather than actively rehabilitate them. Furthermore, the therapy was applied relatively unselectively to all care home residents, rather than specifically targeted towards care homes residents with stroke-related disabilities. A cluster randomised trial, which evaluated the effect of OT compared to usual care over 3 months in 118 residents with a stroke-related disability at 12 care homes, found that residents who received OT were less likely to deteriorate in their ability to perform activities of daily living [10]. From baseline to 3 months the mean Barthel Activities of Daily Living Index (Barthel index) score had increased by 0.6 (SD = 3.9) in the intervention group, but decreased by 0.9 (SD = 2.2) in the control group. This equated to a difference between the groups of 1.5 and 95% confidence interval of -0.5 to 3.5 (allowing for a cluster design). The difference between the groups in Barthel index was maintained at 6 months (i.e., difference of 1.9 and 95% confidence interval of -0.7 to 4.4). The sample size was very small especially when taking into account the high intra class correction (ICC) of 0.37 (Barthel index at baseline), which is consistent with the ICC of 0.39 found in a subsequent pilot study of incontinence care in the same setting [11].

The findings from these studies demonstrate that even modest levels of OT may have detectable and lasting effects on morbidity and possibly mortality. It would, therefore, be appropriate to replicate the study with a larger sample to investigate the clinical impact of OT on activities of daily life in care homes residents with stroke-related disabilities.

In addition to the investigation of clinical impact of OT, a larger sample size will enable a full assessment of the economic impact that OT has on providing health care. Previous work in Canada [12] and in the UK [13] investigated the cost of OT in care homes, based on cost-consequence analyses. The Canadian study studied two types of OT and physiotherapy intensities, which compared 1 therapist to 50 bed ratio to 1 therapist to 200 bed ratio. Improvements in functional outcome measures favoured OT and physiotherapy delivered at the 1:50 ratio, which resulted in reduced direct nurse time and equated to an annual saving of 283 Canadian dollars per resident [12]. The study conducted in the UK, examined the effect of OT on levels of depression and quality of life in care homes residents [13]. It was found that, at 2005 levels, the net cost of providing the OT service was 16 British pounds per resident per week. However, it was suggested by the authors that OT might have resulted in a reduction in overall health costs [13]. Both studies suggest that providing OT to residents in a care homes incurs an initial cost to health care providers, but generates savings in the long-term through the improvement of functional outcomes of residents without stroke-related disabilities [12,13]. There is, therefore, a need to analyse the economic impact of OT on residents with stroke-related disabilities in care homes.

The purpose of this study is to conduct a large scale cluster randomised control trial to evaluate the effects of the provision of OT, which include task related training, the provision of adaptive equipment, minor environmental adaptations and staff education, compared to usual care, on activities of daily living, mobility, depression and quality of life for residents with stroke-related disabilities in care homes. Allocation of therapy cannot be concealed from the carers and/or residents so, to minimise contamination of intervention, the unit of randomisation will be the care home. Furthermore, we aim to conduct a health economic evaluation of the effect of the provision of OT services has on the health care system compared to usual care. Given the findings of previous studies on clinical [1,9-11] and health economic [12,13] impact of OT compared to usual care in the UK [5,8], it is hypothesised that the provision of OT services will have a favourable impact on activities of daily living, and reduce long-term costs to health care providers.

## Methods/Design

### Design

This study is a pragmatic stage III cluster randomised controlled trial with health economic evaluation. The flow diagram for this trial is presented in Figure 1. and follows the CONSORT extension for cluster randomised trials [14].

**Figure 1 F1:**
[figure not shown]
Flow diagram of the progress of clusters and individuals through phases of the trial.

### Setting

Care homes for older people in the UK from Birmingham, Bangor, Coventry, Portsmouth, Nottingham, Central Lancashire, Peninsula, Staffordshire and Wolverhampton areas. We will include all funding models of homes (i.e. private, charitable, not for profit and local authority). Homes for people with learning disabilities or drug addiction will be excluded from the study.

### Recruitment and consent

#### Care homes

Care home managers will be approached and provided with information about the study. They will be given a full oral explanation of the study, a leaflet describing OT and study information sheets. Care home managers will be asked to give written agreement for their home to participate in the study. Following this, residents will be recruited individually.

#### Residents

Care home managers will assist to identify potential participants. Participants must be resident in a care home and have a history of stroke or transient ischaemic attack (TIA). All efforts will be made to include participants with communication and cognitive impairments, because this will more accurately reflect the population characteristics. Participants will be excluded from the study if they are receiving end-of-life care (with life expectancy < 6 months). Care home members of staff will search residents’ notes to determine a diagnosis of stroke or TIA. If required, we will confirm this diagnosis with general practice records. When a potential participant is identified as being eligible for the study, they and (where appropriate) their family (outlined in the UK’s Mental Capacity Act 2005 [15]) will be approached by a senior member of the care home staff, a research network nurse or therapist, general practitioner or geriatrician, and will be asked if they are interested in participating in a research study. Prospective participants (and their family) will be given a full explanation of the study. This will include discussion of the treatment options in the trial and the manner of treatment allocation. Potential participants and their family will be given a participant information sheet, or a consultee information sheet and the UK Clinical Research Network’s 2007 [16] publication on ‘Understanding Clinical Trials’ to read. They will be given sufficient time to decide (at least 24 hours) whether they would like to join the study. This may take a few days if relatives only visit at weekends for example. Residents will then be asked to sign the consent form. If the resident is considered to be incapacitated, according to the Mental Capacity Act 2005 guidelines [15], a family member (consultee) will be approached for consent. The participant’s general practitioner will be informed, if the patient or consultee consents, in writing of their participation in the trial. Research nurses from NHS research networks will assist in the recruitment and consent processes.

### Randomisation

Homes and participants will be recruited and consented into the study before the randomisation process commences to reduce bias [17,18]. Homes will be stratified by residential care homes providing personal care and homes providing additional nursing care. Once the study co-ordinator ([name]) receives confirmation from the assessors that all residents in a participating home have given their consent and completed a baseline assessment, the homes will be grouped and randomised (50:50) to receive either the OT intervention or control (usual care). The assignment of cluster to either the OT intervention or control arm of the study will be conducted by the study co-ordinator. They contact the managers of the homes directly and make arrangements for the occupational therapist to visit the care home to commence the intervention. The allocation sequence will be generated by a statistician ([name]) using blocked randomisation within strata (centre and type of home; residential, nursing) at the Primary Care Clinical Research and Trials Unit at the University of Birmingham, independent from the research team. The details of the sequence will be unknown to any of the assessors or to the study co-ordinator. Allocation will be concealed from the independent assessors, but it is not possible to mask the treating therapists or residents from the intervention. The success of blinding will be evaluated at each follow-up stage by asking the assessors to record if the allocation has been revealed to them.

### Intervention

We developed an OT intervention package for residents in a care home using evidence and consensus from a previous study [19]. The OT intervention will be provided by qualified occupational therapists and assistants and will be targeted towards improving independence in activities of daily living, such as feeding, dressing, toileting, bathing, transferring and mobilising. Adaptive equipment will be provided as part of the study and will include personal items, such as adapted cutlery and walking aids. Furthermore, adaptations to the individual's environment might need to be made, such as chair raisers, bed levers, raised toilet seats or grab rails. When adaptive equipment or adaptations to the environment have been provided to the resident, the occupational therapist will demonstrate to them and the care staff how to use the equipment effectively, whilst adhering to safety regulations. The frequency and duration of the OT will be dependent on the resident and therapist’s agreed goals (within the framework of the home). In the pilot study, the number of face-to-face sessions ranged from 1 to 25 per resident over a three-month period (median time = 8.5 hours and mean time = 4.7 hours), dependent on the individual needs of the resident [19]. The OT intervention will follow a ‘client centred approach’ [20] and will include a continuous process of assessment, treatment and reassessment. In line with current evidence on effective treatment, the OT intervention will adopt a task-specific training approach [21]. Treatment logs have been developed in which the dose and focus of OT intervention can be documented. This will allow for accurate costing for health care services to residents in care homes to be calculated. Care homes in the control arm of the study will continue to provide their usual care to residents (i.e. continue providing (or not) any therapy as they would do usually).

### Training for care home staff

Specific training will be given for staff involved in the care of the residents receiving active therapy. In addition, all intervention homes will be offered a group training session on the key principles of OT by the occupational therapist. A half-day group training session for care home staff has been developed and summarised, on the facilitation of independent daily living activities and mobility of residents [22].

Care homes in the control arm will receive similar training, but only after the 12 month follow-up assessment has been completed. It is anticipated that delivering the training to the control group will facilitate compliance and reduce loss to follow-up in the control group. This, in turn, will reduce the potential bias during the follow-up period [19].

### Outcome measures

#### Demographic data

Information recorded by a member of staff from the care home about the resident will include age, gender, current medication intake and date, type and side of stroke. Furthermore, at baseline a trained assessor will administer the Sheffield Screening Test for Acquired Language Disorders, to assess receptive/expressive aphasia [23], and the mini mental state examination to assess cognitive function [24]. Finally, data on resource use will be recorded through logs and collected from health and social care services to conduct a health economic evaluation for both interventions delivered during this study.

#### Primary outcome measure

The primary outcome measure is the Barthel Activity of Daily Living Index [25], which is a commonly used measure of independent self-care in people who survived a stroke [26,27]. Furthermore, the Barthel index assesses specific aspects of self care targeted by the therapy. A change of two points on this scale is widely accepted as being clinically meaningful [28]. The Barthel index can be completed by the resident or with assistance from a member of staff.

#### Secondary outcome measures

Secondary outcome measures will assess mobility, mood, safety, quality of life and costs. Mobility will be assessed with the Rivermead mobility index [29], which is a 15-item measurement of functional mobility. The geriatric depression scale [30] will be administered to measure mood. The full 30-item version will be used as standard, but in cases where residents are unable to self complete or follow and interview the informant version will be filled out. Quality of life is measured by the EQ-5D [31], which is a well established measure for evaluating patients preference. Costs will be estimated based on resource usage log and weighted by unit costs. This will include visits to hospital and include in- and out-patient appointments, allied health professionals time, general practitioner visits, provision of care in a care home, adaptive equipment, minor environmental adaptations and staff education. Unit costs will be obtained from the national health and social care services reference costs and personal social services research unit [32]. Additionally, any adverse events will be recorded in participant logs and will include a fall or equipment failure leading to an injury requiring a visit to a hospital or general practitioner.

#### Assessment schedule

An overview of the assessment schedule is given in Table 1. Baseline assessments will be conducted prior to randomisation to reduce possible recruitment bias repetition [33]. The primary measurement point will be at 3 months after randomisation and follow-up assessments will be conducted at 6 and 12 months prior to randomisation. Data will be collected from participants where they are currently residing. If a participant moves to another home between assessments, then the assessors will attempt to collect follow-up data.

**Table 1 T1:** Proposed assessment schedule

**Assessment**	**Time of administration**			
	Baseline	3 months	6 months	12 months
Demographics	✓			
Sheffield Screening Test*	✓			
Mini Mental State Examination	✓			
Barthel Activity of Daily Living Index	✓	✓	✓	✓
Rivermead Mobility Index	✓	✓	✓	✓
Geriatric Depression Scale	✓	✓	✓	✓
EQ-5D	✓	✓	✓	✓
Resource Use Log		✓	✓	✓
Adverse Event Log		✓	✓	✓

*Full name of the test is Sheffield Screening Test for Acquired Language Disorders.

### Sample size

A sample of 330 residents in each arm will be sufficient to identify a clinically meaningful 2-point change in the Barthel index. This estimate is based on a standard deviation of 3.7 [10], 90% power, 5% level of significance and an ICC of 0.4 [10,11]. Given that the trial will be a cluster randomised trial, it is predicted that 33 homes with 10 residents in each will be required in each arm of the study. Based on the attrition rate of 26% from a previous study [10], it is predicted that 45 homes with 10 residents in each will be required in each arm of the study (i.e., 900 residents in total).

### Statistical analysis

Baseline characteristics of participants will be tabulated by treatment arm. Items will include demographic details of residents, past medical history, questionnaires; and breakdown of the number of care homes and cluster size.

#### Primary analysis

The primary outcome is the mean Barthel index score at the 3 month follow-up. A mixed model analysis will be used to compare Barthel index scores between the intervention and control groups. The primary analysis will be adjusted by care home (as a random factor), baseline Barthel index score, and stratification factors: centre and type of care home (nursing, residential). Participants that die before their follow-up date will be given a Barthel index score of zero at all subsequent follow-ups. In addition, participants will be categorised into 3 outcome groups based on an individual’s change in Barthel index score at 3 months from baseline (below 0 or death = ‘poor’, 0 to 1=’moderate’, 2 and above=’good’). A non-linear mixed effects model will be used to compare this ordinal outcome between the groups. Adjustments will be made for care home (random), centre and type of care home (fixed).

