#### Secondary analysis

To identify any longer term effects, a repeated measures mixed model analysis of the primary outcome will be undertaken, comparing groups across all time points. The analysis will include adjustment for care home (as a random factor), baseline Barthel index score, and stratification factors: centre and type of care home. Similar analyses will be performed for mobility, mood and quality of life.

The number of falls will be compared using a Poisson or negative binomial model, with adjustments for care home, centre and type of care home as previously described. A sensitivity analysis of the outcomes will be performed to examine the potential effect of missing data. This will include best case, worst case and multiple imputation methods.

Analysis will be by intention to treat, whereby residents will be analysed according to the intervention to which they are randomised, regardless of whether they comply with the treatment. All participants irrespective of when they die, withdraw or are lost will be included in the arm to which they were randomised, including those that die after consent but prior to randomisation. Those participants that move home will be analysed by the home they were originally randomised to. Analyses will be performed using Stata (StataCorp,. Texas, USA) and SAS software (SAS Institute Inc., Cary, NC).

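### The supplementary ordinal analysis of Barthel change is the only Barthel model whose stated covariates omit baseline Barthel, although the category reached depends on baseline

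*Protocol article*

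**What the plan says.** The protocol article specifies three analyses of the Barthel score, each with its own adjustment sentence.

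- **Linear mixed model at 3 months (Primary analysis):** "The primary analysis will be adjusted by care home (as a random factor), baseline Barthel index score, and stratification factors", the factors being centre and type of home.
- **Ordinal mixed model at 3 months (Primary analysis):** introduced as an addition to the mean comparison. Change from baseline is cut into three groups ("below 0 or death = ‘poor’, 0 to 1=’moderate’, 2 and above=’good"), and the adjustment sentence reads "Adjustments will be made for care home (random), centre and type of care home (fixed").
- **Repeated-measures mixed model (Secondary analysis):** "The analysis will include adjustment for care home (as a random factor), baseline Barthel index score, and stratification factors: centre and type of care home".

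Deaths are scored at zero: "Participants that die before their follow-up date will be given a Barthel index score of zero at all subsequent follow-ups". The Randomisation section stratifies homes by centre and type of home, not by Barthel score. The Background reports a "high intra class correction (ICC) of 0.37 (Barthel index at baseline") in the earlier trial, and the Sample size section plans with 0.4.

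**The concern.** The ordinal model is the only Barthel analysis whose covariate list leaves out baseline Barthel, and no reason is given. This is not a detail left to an analysis plan, because the article states the list.

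One might think that baseline is already dealt with because the outcome is change. It is not. The outcome is a coarse cut of change on a bounded, imperfectly repeatable score, so the chance of each category still varies with the starting score. Two residents with the same prognosis but different starting scores can have different chances of being graded poor.

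Two things are at stake. In the one trial actually run, the ordinal odds ratio will move with whatever baseline difference chance produces between the arms, and clustering makes that difference larger than under individual randomisation. A strong prognostic variable that is already collected also goes unused. The ordinal and linear results, reported under the same heading, could then differ for a reason unrelated to treatment.

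**Working it through.** **1. Reproduce the plan's own figure.** Inputs from Sample size: "This estimate is based on a standard deviation of 3.7 [10], 90% power, 5% level of significance and an ICC of 0.4 [10,11"], and a target difference of 2 points. Two-sided testing is assumed.

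- Per arm without clustering: 2 × (3.7 × (1.960 + 1.282) / 2)² = 71.9, so 72.
- Design effect: 1 + (10 − 1) × 0.4 = 4.6.
- 72 × 4.6 = 331, against 330 stated (33 homes of 10).
- Attrition: 33 / (1 − 0.26) = 44.6, so 45 homes per arm, as stated.

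The planning figures reproduce and are not in question.

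**2. Chance difference in mean baseline Barthel.** In units of the baseline SD, SE = √(2 × design effect / residents per arm).

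- 45 homes of 10, ICC 0.4: √(2 × 4.6 / 450) = 0.143.
- Same homes, ICC 0.37 (design effect 1 + 9 × 0.37 = 4.33): √(2 × 4.33 / 450) = 0.139.
- 33 homes of 10, ICC 0.4: √(2 × 4.6 / 330) = 0.167.
- 450 individually randomised residents per arm: √(2 / 450) = 0.067.

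With 45 homes per arm, the chance of a gap above 0.1 SD is 48% (13% under individual randomisation). Above 0.2 SD it is 16% (0.3%).

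The article gives no baseline SD. The planning SD of 3.7 is used below, with an assumed range up to 6:

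| Baseline SD | SE of gap (points) | 95% range | P(gap > 1 point) |
|---|---|---|---|
| 3.7 | 0.53 | ±1.04 | 6% |
| 5 | 0.71 | ±1.40 | 16% |
| 6 | 0.86 | ±1.68 | 24% |

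These use the full ICC. Stratifying by centre and type of home, and adjusting for both, would lower them by an amount the article does not allow one to compute.

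**3. Dependence of category on baseline.** The floor needs no simulation: if 0 is the lowest score, as its use for deaths suggests, a resident starting at 0 cannot have a negative change and is poor only by death.

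For the rest of the scale, an illustrative simulation with no treatment effect was run. All its inputs are assumed: a 0–20 scale, baseline mean 6 or 8, baseline SD 3.7 or 6, mean decline 0.5, residual SD 3, 8% deaths unrelated to baseline, and a follow-up-on-baseline slope of 0.8 to 1.0.

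- Baseline 0: P(poor) = 0.08, the assumed death rate.
- Baseline 1–4: P(poor) = 0.41 to 0.54.
- Baseline 15–18: P(poor) = 0.73 to 0.77 at slope 0.8, but 0.54 to 0.55 at slope 1.0.

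The floor effect is present throughout. The gradient above it depends on how much scores regress.

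**4. Effect on the odds ratio.** In the same null simulation, the arm with the higher baseline looks worse. A gap of one SE (0.53 to 0.86 points) gave an odds ratio for poor of 1.02 to 1.12. A gap of 1.96 SE gave 1.03 to 1.25.

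A separate illustration used proportional-odds fits (330 per arm, mean 8, SD 5.5, carry-over 0.85, 150 replicates). A 1-point gap moved the log odds ratio by −0.10, and adjusting for baseline returned it to about 0. With a real effect and no gap, adjustment raised z from 3.43 to 3.62, a factor of 3.62 / 3.43 = 1.06. These fits should not be read as reproducing the protocol's mixed model.

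**5. Scale of that shift.** For 660 residents in three equal categories, the unclustered SE of a proportional-odds log odds ratio is about √(12 / (660 × (1 − 3 × (1/3)³))) = √(12 / 586.7) = 0.14. A shift of 0.10 is then about 0.7 SE, and less once clustering widens the SE.

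**The case against.** The strongest defence is that this is a supporting analysis. The primary outcome is the 3-month mean, that model adjusts for baseline, and the sample size rests on it. Homes are randomised after consent and baseline assessment, so the unadjusted ordinal comparison is fair on average. The outcome is already a change score, and the model includes home, centre and type of home. All of this stands except the point about the change score, which the floor and regression to the mean defeat.

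Four stronger readings are tempting, and the article does not support them:

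- **That a material baseline imbalance is likely.** At SD 3.7 a gap above 1 point has about a 6% chance, and a figure near 20% needs an assumed SD of about 5.5. A 2-point gap is rarer still: 2 / 0.53 = 3.8 SE at SD 3.7, and 2 / 0.79 = 2.5 SE at SD 5.5.
- **That the ordinal result is biased.** It is not biased in expectation. The issue is the conditional shift in the realised trial.
- **That residents near the top of the scale can never be good.** This needs a maximum score, which the article does not state.
- **That the cut-points are inconsistent because a 1-point fall is poor while a 1-point gain is only moderate.** The Primary outcome measure section calls 2 points meaningful, and the good category uses exactly that threshold. Grouping any deterioration with death matches the poor-outcome definition cited in the Background. Symmetric cut-points would be a preference and would redefine the outcome.

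**Conclusion.** The point holds as a modest weakness in a supplementary analysis. The omission is explicit, has no stated reason, and is out of line with the other two Barthel models. Category membership depends on baseline even with no treatment effect.

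The SE of the chance baseline difference is about 0.14 SD, or roughly 0.5 points at SD 3.7 before any reduction from stratification. This is about twice what individual randomisation would give (0.143 / 0.067 = 2.1). The resulting shift in the ordinal odds ratio is likely to be within its sampling error, and the precision lost is small (about 6% in z in one assumed scenario).

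The SE in SD units rests on the article's own ICC and cluster sizes. Its conversion to points assumes that 3.7 approximates the baseline SD. The floor argument assumes that 0 is the lowest score. The odds-ratio shifts rest on simulation inputs that the article does not give, so they show direction and order of magnitude only. The primary mean comparison is unaffected.

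**What to change.** In Primary analysis, extend the ordinal model's adjustment sentence so that baseline Barthel score enters as a fixed covariate alongside centre and type of home, with care home still random. This matches the linear and repeated-measures models. If the omission was deliberate, state the reason instead. Leave the three outcome categories as they are.

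The cost is one covariate in one model. Table 1 already schedules the Barthel index at baseline, and no sample-size figure changes. The report should say that the resulting odds ratio is conditional on baseline score, since adding a covariate to an ordinal model changes what the odds ratio describes.
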